## Methods/design

In a prospective randomized controlled intervention study (Fig. 1) patients are randomized 1:1 (mixed randomization scheme using unequal block randomization) between the intervention group and the wait-list control group. Patients are stratified according to baseline stress level (distress thermometer ≥ *vs* < 5 [27]). A total of 120 newly diagnosed adult (>18 years) cancer patients who started first-line treatment (either systemic treatment - including chemotherapy, hormonal treatment or targeted therapy - or radiotherapy) no longer than 12 weeks earlier are included after giving informed consent. Patients who undergo treatment for a first relapse of a tumor previously treated with curative intent are also eligible. Patients are required to read and write in German, have internet-access as well as basic computer skills.

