### Efficacy outcomes

The main efficacy outcome is quality of life (FACT) including assessment of fatigue (FACT-F) [35] at T2. We use the validated German Version **functional assessment of chronic illness therapy-fatigue (FACIT-F)** which is freely available from the website www.facit.org.

To assess anxiety/depression and psychological distress the ** hospital anxiety and depression scale (HADS)** [36] and the **distress thermometer (DT)** in the German version [27] are used, respectively. Patients are stratified based on their level of baseline distress. A score of five or higher at the DT visual analogue scale is a cut-off score for a clinically significant level of distress [27]. To longitudinally describe psychological coping with cancer we use ‘the acceptance and action questionnaire (AAQ)’ in its German version ‘***Fragebogen zur Akzeptanz und Handeln***
**(FAH II)’** [37], which we adapted specifically for cancer patients with three additional items concerning their coping with the disease.

The online support program STREAM is not designed to support suicidal patients in acute crises. For safety reasons, **suicidal tendency** is assessed by the single suicide item out of the Beck Depression Inventory (BDI) [38]. Patients with a score higher than one are contacted by telephone to reassess suicidal ideation and, if needed, patients are instructed to call for local psychiatric support.

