### Statistical analyses and sample size calculation

Based on previous studies [43] including recent data on cancer patients [44], a difference of nine points in the FACT score is both, clinically significant and realistic. In order to demonstrate a 9-point difference between baseline and T2 (after 8 weeks) in the intervention group with a statistical power of 0.80 at a significance level of 0.05 (two-sided), 60 participants are needed in each of the two conditions. We assume normally distributed data in both groups with a standard deviation of ±18 [45]. Data preparation of all continuous dependent variables will include tests for normality, homogeneity of variances, and examination of outliers. If not normally distributed, variables will be subjected to adequate transformation. Intent-to-treat samples will be used to analyze data. The choice of statistical approach depends on the amount of missing data at T2 and T3. If less than 12 % of data are missing, the Last Observation Carried Forward (LOCF) method will be applied to estimate effects. Then, the outcome will be computed with an analysis of covariance (ANCOVA), using the pre-scores as a covariate and the post-scores as the dependent variable. If more than 12 % of data are missing, we will use linear mixed models. This method is recommended for intent-to-treat-analyses with a high amount of dropouts due to its potential to reduce bias caused by missing data. Regression analyses will be used to identify predictors of treatment outcome.

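### The stated efficacy models do not name the randomisation stratum (baseline distress); adding it is a minor, nearly free alignment that removes a possibly oversized standard error

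*Protocol article*

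**What the plan says.** **Randomisation.** Under Methods/design, allocation is 1:1 in blocks of varying size, and "Patients are stratified according to baseline stress level", with the distress thermometer (DT) split at 5. Efficacy outcomes repeats it: "Patients are stratified based on their level of baseline distress". The Discussion again calls distress a stratification factor.

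**Main outcome.** Efficacy outcomes states: "The main efficacy outcome is quality of life (FACT) including assessment of fatigue (FACT-F) [35] at T2". The pre-score for this outcome is therefore baseline FACT, not the DT.

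**Analysis.** Statistical analyses and sample size calculation gives two branches. Below 12 % missing data, last observations are carried forward and an ANCOVA is fitted, "using the pre-scores as a covariate and the post-scores as the dependent variable". Above that, "If more than 12 % of data are missing, we will use linear mixed models", with no covariates listed. No section places the DT stratum in an efficacy model.

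**The concern.** A factor used to stratify randomisation is normally carried into the analysis. Stratifying removes chance imbalance in that factor between the arms, so the treatment estimate varies less from trial to trial. A model without the factor leaves its effect in the residual variance and computes the standard error as if the imbalance could still occur. If the factor predicts outcome beyond the covariates already fitted, the reported standard error is larger than the estimate's true variability. Confidence intervals are then a little wide and the test a little conservative.

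The article gives some reason to think the factor is prognostic: the Background (Impact of cancer on mental health) links distress with lower quality of life. What matters here is narrower, namely how much the DT stratum predicts T2 FACT once baseline FACT is in the model. The article does not say.

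The two branches add a smaller issue. Unless the covariates are fixed for both, the adjustment set could differ according to which side of 12 % the missing data fall.

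**Working it through.** **Inputs from the article** (Statistical analyses and sample size calculation): difference 9 FACT points, SD 18, two-sided alpha 0.05, power 0.80, 60 per arm.

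**Assumed, because the article gives neither:** r, the correlation of baseline with T2 FACT; p, the partial correlation of the DT stratum with T2 FACT given baseline FACT.

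**Step 1: the plan's own figure.** Two-group comparison, normal approximation:

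n per arm = 2 × 18² × (1.96 + 0.8416)² / 9² = 62.8, so 63 (64 with the t distribution), against 60 stated.

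Power at 60 per arm is 0.782 (normal) or 0.775 (t). The stated 60 is not reproduced exactly. That is a separate matter, not caused by the omitted stratum and not evidence for this point. Adjusting for the pre-score alone would more than offset it: 58 per arm suffice at r = 0.3 and 48 at r = 0.5.

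**Step 2: nominal effect of adding the stratum.** Residual SD is 18 × √(1 − r²) with the pre-score, multiplied by a further √(1 − p²) with the stratum. The residual variance therefore falls by p²: 0, 1, 4 and 9 % for p = 0, 0.1, 0.2 and 0.3. Power is Φ(9 / SE − 1.96), with SE = SD × √(2/60).

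Example, r = 0.5:
- Pre-score only: SD 15.59, SE 2.846, power 0.885.
- With stratum at p = 0.3: SD 14.87, SE 2.715, power 0.912.

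| r | pre-score only (p = 0) | p = 0.1 | p = 0.2 | p = 0.3 |
|---|---|---|---|---|
| 0.3 | 0.819 | 0.823 | 0.834 | 0.853 |
| 0.5 | 0.885 | 0.888 | 0.898 | 0.912 |
| 0.6 | 0.928 | 0.931 | 0.937 | 0.948 |

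The gain is 0 to about 3 points.

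**Step 3: simulation under stratified allocation.** Step 2 treats the model standard error as the true variability, which is not right when randomisation has already balanced the stratum. Trials of 120 patients were simulated 5,000 times per setting. Assumptions: about 60 % of patients in the high-distress stratum, blocks of 4 or 6 within stratum, SD 18, true effect 9. The partial correlation in the first column is that of the underlying continuous distress score; dichotomising it weakens it. Each cell gives the ANCOVA without / with the stratum.

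| Setting | Mean model SE | Actual SD of estimate | Power | Type I error |
|---|---|---|---|---|
| r = 0.6, partial 0 | 2.633 / 2.635 | 2.617 / 2.616 | 0.927 / 0.926 | 0.041 / 0.040 |
| r = 0.6, partial −0.14 | 2.634 / 2.620 | 2.616 / 2.617 | 0.925 / 0.925 | 0.048 / 0.049 |
| r = 0.6, partial −0.29 | 2.631 / 2.571 | 2.593 / 2.586 | 0.931 / 0.935 | 0.048 / 0.053 |
| r = 0.5, partial −0.42 | 2.852 / 2.695 | 2.717 / 2.704 | 0.890 / 0.911 | 0.039 / 0.050 |

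The simulated type I errors carry a Monte Carlo standard error of √(0.05 × 0.95 / 5000) = 0.003, so small differences between them should not be read closely. A direct check from the standard errors in the last row: 1.96 × 2.852 / 2.717 = 2.057, a two-sided level of 0.040, in line with the simulated 0.039.

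The actual spread of the estimate hardly moves when the stratum is added. What changes is the reported standard error, which without the stratum exceeds the true spread by 1.5 % (2.631 / 2.593) in the third row and 5 % (2.852 / 2.717) in the fourth.

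**The case against.** **The article never says that the pre-score is the sole covariate.** It is a condensed report, the ANCOVA applies only below 12 % missing data, and an unseen full protocol or analysis plan may include the stratum. This stands as a limit: the two sections do not contradict each other, and a reader should not infer that the stratum has been ruled out. It does not dispose of the point. The article does state a model, with its outcome and covariate, and that model can be improved at almost no cost.

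**Baseline FACT may already carry the distress information.** This also stands. If p is 0 there is nothing to gain, so the range must start at 0.

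**Little real precision is at stake.** A reader might infer that omitting the stratum throws away the benefit of stratifying, or wastes the equivalent of up to 12 patients (120 / 0.91 = 131.9, against 120 / 0.99 = 121.2 at p = 0.1). The simulation does not support that. Balance comes from the allocation and survives whatever model is fitted, and the estimate's SD was 2.593 without and 2.586 with the stratum. The patient equivalents describe the nominal standard error only.

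**The DT as an outcome.** A reader might expect a larger gain there. The article gives no support for this: the stratum is a cut of baseline DT itself, so adjusting for continuous baseline DT already captures most of it.

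**Conclusion.** The point holds as a minor one. Randomisation is stratified by baseline distress, and neither stated efficacy model names that stratum. If the stratum is prognostic beyond baseline FACT, the reported standard error is somewhat too large and the test slightly conservative.

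The size is small and rests on assumed correlations: 0 to 9 % of residual variance and about 0 to 3 power points at 60 per arm, for p from 0 to 0.3 and r from 0.3 to 0.6. At the stronger underlying correlation of −0.42 the simulated gain was still about 2 points (0.890 to 0.911) for a 9-point effect, and 4 points (0.683 to 0.723) had the true effect been 7.

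A reader might go further and infer a biased treatment effect or an invalid test. Neither follows. The omission does not bias the estimate, and its effect on the type I error is downward.

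**What to change.** State that all between-arm efficacy models, both the ANCOVA and the linear mixed model, include arm, the baseline value of the outcome and the randomisation stratum (DT 5 or more versus below 5). For the DT as an outcome, keep continuous baseline DT and add the stratum for consistency, expecting little further gain. If an unseen analysis plan already does this, confirming it is enough.

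The cost is one degree of freedom; the covariate is collected on every patient at baseline. Trial status reports 80 of 120 patients recruited, so on that date the model could still be fixed before analysis. Adding the covariate after results are known would be open to the charge of being data-driven.

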**Methods/design:**

In a prospective, wait-list controlled trial 120 newly diagnosed cancer patients will be included within 12 weeks of starting anti-cancer treatment and randomized between an immediate (intervention group) or delayed (control group) 8-week, web-based intervention. The intervention consists of eight modules with weekly written feedback by a psychologist (“minimal-contact”) based on well-established stress management manuals including downloadable audio-files and exercises. The aim of this study is to evaluate efficacy in terms of improvement in quality of life (FACT-F), as well as decrease in anxiety and depression (HADS), as compared to patients in the wait-list control group. A sample size of 120 patients allows demonstrating a clinically relevant difference of nine points in the FACT score after the intervention (T2) with a two-sided alpha of 0.05 and 80 % power. As this is the first online stress management intervention for German-speaking cancer patients, more descriptive outcomes are equally important to further refine the group of patients with the largest potential for benefit who then will be targeted more specifically in future trials. These descriptive endpoints include: patients’ characteristics (type of cancer, type of treatment, socio-demographic factors), dropout rate and dropout reasons, adherence and satisfaction with the program.

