**Discussion:**

New technologies open new opportunities: minimal-contact psychological interventions are becoming standard of care in several psychological disorders, where their efficacy is often comparable to face-to-face interventions. With our study we open this field to the population of newly diagnosed cancer patients. We will not only assess clinical efficacy but also further refine the target population who has the most potential to benefit. An internet-based minimal-contact stress management program might be an attractive, time- and cost-effective way to effectively deliver psychological support to newly diagnosed cancer patients and an opportunity to include those who currently are not reached by conventional support.

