### Objective and research questions

In a prospective randomized wait-list controlled trial we assess the efficacy of a minimal-contact online intervention in newly diagnosed cancer patients. More specifically, we assess whether patients who undergo the online intervention report a better quality of life (FACIT-F), are less anxious and depressive (HADS-D), less stressed (DT), and cope better with their disease (FAH II) as compared to patients in the wait-list control group. This is the first online stress management intervention in German for cancer patients (STREAM: **STRE**ss **A**ktiv **M**indern). Moreover, since it is novel to recruit patients via the internet rather than face-to-face, we set out to determine patients characteristics for participation and benefit. These descriptive outcomes include: patients’ characteristics (type of cancer, type of treatment, sociodemographic factors), patients’ adherence as well as satisfaction with the program.

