### Discussion

Psychological distress associated with cancer diagnosis and treatment is high. Yet, psycho-oncological support is often lacking –due to barriers on the patients’ side or to insufficient resources on the providers’ side [15]. Online-interventions with regular psychologist-contact (minimal-contact) -already established in several psychological disorders- might reduce this gap. In our prospective, randomized controlled study we assess the first minimal-contact, online stress management program for German-speaking, newly diagnosed cancer patients.

Our study will yield information on the efficacy of the intervention with respect to quality of life and stress/anxiety. In addition, it will show whether cancer patients are ready to use new technologies to further increase the range of treatment options at their disposal, and -even more importantly- whether patients who are in need of support but slip through the net of the current system can be reached. Conversely, the time- (and indirectly the cost-) effectiveness of administering support in a minimal-contact online intervention will be assessed from the providers’ perspective – an outcome with important implications for the health care system.

On a different level, the contribution of various and novel recruitment strategies (flyers, “conventional face-to-face”, internet links, Google Ads, Facebook Ads, You tube) will be described allowing for conclusions for future online study portals.

One of the limitations of the study is the heterogeneity of newly diagnosed cancer patients with respect to tumor type, treatment type and treatment strategies (curative, palliative). However, the distress of a new cancer diagnosis is their common denominator, and a stratification factor. Also, since this is the first online stress management program for newly diagnosed cancer patients, we deliberately aim at reaching a broad population to avoid missing a small but important group of patients with potential benefit from this intervention. The results of this study will allow characterizing the patient population(s) with respect to age, sex, diagnosis and treatment that will then be studied more specifically in follow-up trials. Our trial represents a first step in expanding the much-needed psychological support for newly diagnosed cancer patients towards the promising approaches that come with new technical possibilities which have become integral part of our lives.

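### The aim is to find who benefits most, but the only analysis named for it targets predictors of outcome and does not commit to an arm-by-characteristic comparison

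*Protocol article*

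**What the plan says.** The aim appears in four places in the protocol article.

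- Abstract, Methods/design: the descriptive outcomes are meant to "further refine the group of patients with the largest potential for benefit who then will be targeted more specifically in future trials".
- Abstract, Discussion: the trial will "further refine the target population who has the most potential to benefit".
- Objective and research questions: "we set out to determine patients characteristics for participation and benefit".
- Discussion: "The results of this study will allow characterizing the patient population(s) with respect to age, sex, diagnosis and treatment", with those populations then to be studied in follow-up trials.

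The analysis appears once, as the last sentence of Statistical analyses and sample size calculation: "Regression analyses will be used to identify predictors of treatment outcome". Earlier in that section the efficacy model is an ANCOVA "using the pre-scores as a covariate and the post-scores as the dependent variable", or a linear mixed model if more than 12% of data are missing. The article nowhere mentions an interaction, a moderator or effect modification.

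**The concern.** A predictor of outcome and a modifier of the treatment effect are different things. Patients treated with curative intent, for example, may score better at T2 whether or not they used the programme. A regression of outcome on characteristics would pick them out, yet they may gain no more than anyone else. To show that a group benefits more, its difference between intervention and wait-list must be compared with the same difference in other groups.

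The design allows this comparison at T2. By T3 the wait-list group has had the delayed intervention (Assessments), so T2 is the only randomised treated-versus-untreated contrast. The analysis sentence does not say that this contrast will be used. At stake is which patients the follow-up trials are built around.

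**Working it through.** **Inputs from the article** (Statistical analyses and sample size calculation): difference 9 points, SD 18, 60 per arm (N = 120), two-sided alpha 0.05, power 0.80. The 9 points is the effect the article calls meaningful and attainable: "a difference of nine points in the FACT score is both, clinically significant and realistic".

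**Assumptions, not in the article:** a two-level characteristic split 50/50, 30/70 or 20/80; a correlation r between baseline and T2 score of 0, 0.5 or 0.7; a difference in effect between subgroups as large as the planned overall effect.

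**The plan's own figure.** For two independent means, n per arm = 2 × (1.96 + 0.84)² × 18² / 9² ≈ 62.8, so 63. With 60 per arm the power is 78%. The planned size is thus close to what the overall between-group effect needs, with nothing spare for subgroup contrasts.

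**Precision of an interaction.** For a subgroup with share s of the sample,

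SE = SD × √(4/(N·s) + 4/(N·(1 − s))), with SD replaced by SD × √(1 − r²) under baseline adjustment.

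Power = Φ(9/SE − 1.96). Detectable difference at 80% power = 2.80 × SE.

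Even split, r = 0: SE = 18 × √(4/60 + 4/60) = 6.57; power = Φ(1.37 − 1.96) = 28%; detectable difference 18.4 points.

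| Split | r | SE | Power for 9 points | Detectable at 80% power | Total N for 9 points |
|---|---|---|---|---|---|
| 50/50 | 0 | 6.57 | 28% | 18.4 | 503 |
| 50/50 | 0.5 | 5.69 | 35% | 15.9 | 377 |
| 50/50 | 0.7 | 4.69 | 48% | 13.2 | 257 |
| 30/70 | 0 | 7.17 | 24% | 20.1 | 599 |
| 20/80 | 0 | 8.22 | 19% | 23.0 | 785 |

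**What a predictor regression would flag.** Simulation with 2,000 runs per case, N = 120, SD 18, even split, average treatment effect 9, no baseline adjustment. Entries are the share of runs with p < 0.05 for the characteristic.

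| True situation | Main effect, both arms | Intervention arm only | Interaction |
|---|---|---|---|
| Prognostic only: 9 points in both arms, same benefit | 77% | 46% | 5% |
| Modifier: −9 in controls, +9 in the intervention arm | 4% | 47% | 78% |
| Modifier: 0 in controls, +9 in the intervention arm | 26% | 48% | 28% |

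A pooled main-effect regression usually flags the characteristic that has no bearing on benefit, and flags the strong modifier at about the chance rate. A regression within the intervention arm flags all three at nearly the same rate and cannot tell them apart. Only the interaction responds to benefit and stays at 5% where benefit is equal.

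**The case against.** The analysis sentence gives no dependent variable, arms, covariates or terms. This is a journal article, and the details of an exploratory regression normally belong in a fuller protocol or analysis plan, which is not shown. A reader might infer that the plan fits main effects only, or ignores the wait-list arm. The article says neither, and interactions are not excluded. The simulation shows what would happen under two models that the article does not specify. This part of the objection stands.

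A reader might also take the abstract to rank finding who benefits level with efficacy. What it ranks that way is a set of descriptive outcomes (patient characteristics, dropout, adherence, satisfaction). Refining the benefit group is the purpose they serve, and much of that material needs no between-arm test. The article also calls itself a first step and leaves confirmation to later trials. That stands too, and it limits the weight of the point.

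Finally, the low power counts against the remedy as well: an interaction test would miss most 9-point modifiers. This is true, and it is why the remedy asks for estimates with intervals and not for decisions by significance.

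Two things remain. The mismatch is not a matter of missing detail, because the article names a target (predictors of outcome) that differs from its stated aim (benefit). And the Discussion's promise about what the results will show is the article's own, which no unseen model specification could make good at this sample size.

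**Conclusion.** The point holds as a mismatch between aim and stated analysis, together with an overclaim. Read as worded, the analysis targets prognosis and does not commit to the contrast that defines benefit, so it could point follow-up trials at patients who would have done well anyway. It would be too strong to say that it will do so: that requires both that interactions are left out and that main effects are then read as benefit, and the article states neither. The primary T2 comparison is not affected.

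On size, 120 patients give roughly 19% to 48% power for a 9-point difference in effect over the splits and correlations tabulated. At an even split without baseline adjustment, the detectable difference is 18.4 points, about twice the planned overall effect. These figures rest on the article's SD and N and on the assumed splits and correlations. The change is worth making before analysis, but it concerns an exploratory aim.

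**What to change.** In Statistical analyses and sample size calculation, replace the predictor sentence with wording such as: *Effect modification is examined at T2 in both randomised arms by adding arm-by-characteristic interactions to the primary model for a short pre-listed set of baseline variables (for example distress stratum, age, sex, diagnosis, and curative or palliative setting). Estimates with 95% confidence intervals are reported as exploratory. Main-effect predictors are reported as prognostic only.* If the mixed model is used, the interaction should be expressed as the contrast at T2.

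In the Discussion, change the claim that results will allow these populations to be characterised to one that they will generate hypotheses on them.

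The listed variables are already collected at baseline (Assessments). Trial status gives 80 of 120 recruited, with recruitment continuing, so at that date the list could still be fixed before analysis. The cost is a few model terms, wide intervals to report, and a more modest claim.
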